# CRADLE-5: a stepped-wedge type 2 hybrid implementation-effectiveness cluster randomised controlled trial to evaluate the real-world scale-up of the CRADLE Vital Signs Alert intervention into routine maternity care in Sierra Leone—study protocol

**DOI:** 10.1186/s13063-023-07587-4

**Published:** 2023-09-15

**Keywords:** CRADLE, Sierra Leone, Low- and middle-income countries, Pre-eclampsia, Scale-up, Shock, Maternal mortality, Blood pressure, Complex intervention, Stepped-wedge cluster trial

## Abstract

**Background:**

The CRADLE Vital Signs Alert intervention (an accurate easy-to-use device that measures blood pressure and pulse with inbuilt traffic-light early warning system, and focused training package) was associated with reduced rates of eclampsia and maternal death when trialled in urban areas in Sierra Leone. Subsequently, implementation was successfully piloted as evidenced by measures of fidelity, feasibility and adoption. The CRADLE-5 trial will examine whether national scale-up, including in the most rural areas, will reduce a composite outcome of maternal and fetal mortality and maternal morbidity and will evaluate how the CRADLE package can be embedded sustainably into routine clinical pathways.

**Methods:**

CRADLE-5 is a stepped-wedge cluster-randomised controlled trial of the CRADLE intervention compared to routine maternity care across eight rural districts in Sierra Leone (Bonthe, Falaba, Karene, Kailahun, Koinadugu, Kono, Moyamba, Tonkolili). Each district will cross from control to intervention at six-weekly intervals over the course of 1 year (May 2022 to June 2023). All women identified as pregnant or within six-weeks postpartum presenting for maternity care in the district are included. Primary outcome data (composite rate of maternal death, stillbirth, eclampsia and emergency hysterectomy) will be collected. A mixed-methods process and scale-up evaluation (informed by Medical Research Council guidance for complex interventions and the World Health Organization ExpandNet tools) will explore implementation outcomes of fidelity, adoption, adaptation and scale-up outcomes of reach, maintenance, sustainability and integration. Mechanisms of change and contextual factors (barriers and facilitators) will be assessed. A concurrent cost-effectiveness analysis will be undertaken.

**Discussion:**

International guidance recommends that all pregnant and postpartum women have regular blood pressure assessment, and healthcare staff are adequately trained to respond to abnormalities. Clinical effectiveness to improve maternal and perinatal health in more rural areas, and ease of integration and sustainability of the CRADLE intervention at scale has yet to be investigated. This trial will explore whether national scale-up of the CRADLE intervention reduces maternal and fetal mortality and severe maternal adverse outcomes and understand the strategies for adoption, integration and sustainability in low-resource settings. If successful, the aim is to develop an adaptable, evidence-based scale-up roadmap to improve maternal and infant outcomes.

**Trial registration:**

ISRCTN 94429427. Registered on 20 April 2022.

## Introduction: background and rationale {6a}

In Sierra Leone (SL), the reduction of maternal and neonatal morbidity and mortality are high priorities of the health sector, in line with the third Sustainable Development Goal [1]. Despite an almost 40% reduction in the maternal mortality ratio (MMR) from 1165 per 100,000 in 2013 to 717 per 100,000 live births in 2019 [2], SL still has one of the highest MMR in the world. One in thirty-one women die during childbirth [3], with a 40 to 60 percent higher risk for teenage mothers [4]. Perinatal mortality is high (34 per 1000 live births), with a stillbirth rate of 24 per 1000 live births [3]. Infants whose mothers die are up to ten times more likely to die within the first two years of life [5].

Data from the CRADLE-3 trial [6] correlate with national statistics; 76% of maternal deaths are caused by haemorrhage, hypertension and sepsis [7]; all of which are marked by abnormalities in blood pressure (BP) and heart rate (HR). If deteriorating vital signs are detected early, maternal morbidity and mortality are preventable with simple, cost-effective interventions that are widely available in SL [6, 8]. However, there are often disparities in access to vital sign assessment and skilled intervention, and delays in delivery and escalation of care [9, 10], varying by geographical area and socio-demographic characteristics.

Vital sign measurement is an international standard part of maternity care. The CRADLE Vital Sign Alert (VSA) device is a hand-held, semi-automated, low-cost BP and HR measuring device with a built-in traffic-light warning system that has been especially developed for use in low-income settings during pregnancy and the postpartum period [11]. The device has additionally been validated as accurate for use in women with preeclampsia [12] and in those who develop low BP from sepsis or haemorrhage [13].

The CRADLE-3 trial [14] investigated the introduction of the CRADLE intervention into routine maternity care in ten clusters across Africa, India, and Haiti. Freetown, SL’s urban capital city, reported a 40% reduction in the primary outcome (at least one of eclampsia, emergency hysterectomy, and maternal death) [odds ratio (OR) 0.60 (95% CI 0.50–0.72), *p* < 0.001] and a 60% reduction in maternal death (risk ratio (RR) 0.37 [95% CI 0.25 to 0.55], *p* < 0.0001) [6]. This trial confirmed that deaths and associated morbidity are avoidable with appropriate triage and escalation. A concurrent process evaluation across all CRADLE-3 trial sites found considerable variation in the implementation, reach, adoption and context; analysis in individual countries was recommended [15].

This evidence base combined with an increased focus on timely maternity triage and escalation led the SL Ministry of Health and Sanitation (MoHS) to advocate for the pilot of the CRADLE intervention across eight out of the county’s sixteen districts between March 2020 and January 2021 (funded by the UK Foreign, Commonwealth & Development Office, the World Health Organization and UNICEF). Full results will be published separately, but in summary, 160 CRADLE Champions and 40 Master Trainers were trained, and 2800 CRADLE devices and 1200 large cuffs distributed. The rollout reached 716 peripheral health unit (PHU) facilities providing maternity care, and rolled out to 2031 frontline healthcare staff, showing high levels of feasibility and acceptability. Strong acceptance from frontline healthcare staff and robust evidence prompted buy-in and advocacy by the MoHS in Sierra Leone for horizontal scale-up of the CRADLE intervention to the rest of the country (Fig. 1).

**Fig. 1 Fig1:**
[figure not shown]
Map of Sierra Leone. Districts which already have the CRADLE intervention are marked (1) and districts included in the CRADLE-5 trial are marked (2). Attribution: Karte: NordNordWest, Lizenz: Creative Commons by-sa-3.0 de

Our set goal is the scale up of the CRADLE intervention to improve access to quality and timely maternity assessment to enable appropriate care for pregnancy hypertension and shock related to obstetric haemorrhage and infection. The remaining eight districts are rural and provide the opportunity to evaluate the impact of CRADLE in this setting, where appropriate triage and referral may have greater impact on outcomes.

This protocol describes the stepped-wedge cluster-randomised controlled trial to evaluate both the clinical impact and scale-up of the CRADLE VSA and training package in Sierra Leone. In-depth context and system specific pilot work highlighted district-specific adaptations and implementation strategies which, alongside our theory of change workshops, has substantially informed the CRADLE-5 trial scale-up strategy [9]. Our aim is to ultimately develop an adaptable, evidence-based roadmap for scale-up in order to achieve sustainable impact on maternal and fetal outcomes. We have been guided by four key principles: systems thinking; a focus on sustainability; the need to determine scalability; and respect for gender, equity and human rights principles [16].

## Hypotheses

We hypothesise that integrating the use of the CRADLE VSA device into routine maternity care and scaling-up focused CRADLE training to the remaining half of SL will increase *availability* of vital signs monitoring equipment, *engage* and *empower* healthcare workers, communities and women to understand the importance of vital sign measure, and enable *reassurance* or alert users and women to when results are abnormal, ensuring prompt life-saving *communication*, *action* and/or *referral* for both mother and unborn baby from the three leading causes of maternal death: obstetric haemorrhage, sepsis and pregnancy hypertension.

## Objectives {7}

The primary objective of the trial is to determine whether real-world scale-up of the CRADLE VSA device and focused education package to community and facility level maternity care in SL is sustainably adopted and reduces a composite of (all-cause) maternal mortality or major morbidity and fetal loss by ≥ 20%.

The trial is complemented by a simultaneous process and scale-up evaluation informed by Medical Research Council guidance [17] and WHO ExpandNet tools [16]. The specific goals of the process and scale up evaluation are to (1) analyse how, and to what extent, the CRADLE intervention has been implemented, (2) assess how the different contexts can influence the implementation process and scale-up strategies and (3) assess the process and sustainability of the scale-up. This will include an evaluation of cost-effectiveness.

## Trial design {8}

### Feasibility phase: January 2022–April 2022

The trial was preceded by a feasibility phase. The eight main trial districts collected primary outcome data to evaluate the methods of data collection and to inform the randomisation programme and sample size calculation. The results were used to optimise the final CRADLE-5 protocol including training materials and implementation strategies for the main trial.

### Definitive stepped-wedge cluster-randomised controlled trial: May 2022 to June 2023

The CRADLE-5 trial is a pragmatic, mixed-methods, multi-district, stepped-wedge cluster-randomised controlled trial of the scale-up of the CRADLE intervention (CRADLE VSA device and CRADLE training package) into routine maternity care settings in SL and will be reported in line with the CONSORT stepped wedge cluster randomised trials update [18]. It will be accompanied by a concurrent process and scale-up evaluation between January 2022 to June 2023.

## Methods: participants, interventions, and outcomes

### Study setting {9}

The study is taking place in SL, a country on the southwestern coast of Africa with a population of 8.8 million [19].

SL is a least developed country according to the OECD list [20] and has one of the highest mortality rates in the world, with a high burden of communicable and non-communicable diseases. It struggles to provide basic universal health coverage, portable water and sanitation. All public health facilities offer free healthcare services to pregnant women, lactating mothers and children below the age of five; however, 72% of women report at least one serious problem in accessing health care for themselves when they are sick; the most commonly cited problem is getting money for treatment (67%) [2]. SL suffers an inadequacy of human resource and diagnostic readiness for health. Nineteen per cent of health facilities have no BP device, and 82% of maternal deaths occurred in a health facility [10]. Latest figures report 0.7 doctors and 7.5 nurses and midwives per 10,000 population [21], well below WHO’s health workforce targets for UHC and SDGs of 23 doctors, nurses and midwives per 10,000. Suboptimal maternal healthcare coverage contributes to preventable deaths, disability and high out-of-pocket spending in a country with an incipient financial crisis, exacerbated by the 2014 Ebola epidemic and further weakened by the COVID-19 pandemic. The capacity and resources to develop and implement national strategies and to produce robust needs-based staffing remain a priority. Our proposed interventions will be evaluated for impact on maternal and fetal outcomes, and cost-effectiveness to take all aspects into account.

The country is divided into five administrative regions (Northern, Southern, Eastern, North-western, and Western) which are further subdivided into 16 districts. Each trial cluster is made up of a specific district in SL; the following eight districts, which have not yet received the CRADLE intervention, were included in the trial: Bonthe, Falaba, Karene, Kailahun, Koinadugu, Kono, Moyamba and Tonkolili. From our selected districts, populations range between 200,781 (Bonthe) to 531,435 (Tonkolili). Bonthe is the smallest, covering an area of 3469 km^2^, whereas Koinadugu is 12,121 km^2^.

Each district comprises a secondary hospital health centre with multiple satellite primary peripheral health units in the community. The total number of peripheral health units per district ranges from 50 in Falaba to 109 in Moyamba. The trial will work across all levels of healthcare facility in the country, reaching the most deprived, remote, and rural communities. Seven of the districts comprise of at least one secondary health facility with multiple satellite primary care centres (called peripheral health units in Sierra Leone) that refer into the secondary hospital. One district (Falaba) does not have a secondary hospital, and referrals from its satellite primary care centres go primarily to the secondary hospital in Koinadugu, as well as to other neighbouring districts.

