### Sample size estimation {14}

Sample size estimation has been provided by the CRADLE senior statistician, using Stata version 13.1 and the methods of Hemming and Girling [28]. The power of the study will depend on three factors: (1) the design (eight groups, six-weekly time periods, around 1000 deliveries/period/centre), (2) the event rate and treatment effect (5% falling to 4%) and (3) the data structure, specifically the intraclass correlation coefficient (ICC) and cluster autocorrelation (CAC) coefficients.

Sample size calculations for longitudinal cluster randomised trials, such as our proposed stepped-wedge trials, necessitate the estimation of the correlation structure underlying the study. This entails assessing both the within-period intra-cluster correlations, which differ from conventional intra-cluster correlations due to their reliance on the period, and the cluster autocorrelation coefficients to account for correlation decay. For the purposes of the power calculation, we assume that there are up to 1000 deliveries per district per six weeks (half the 2000 we consider likely), across eight districts, each observed for 12 months. It is difficult to estimate more accurately at present, as we have no suitable multi-centre, multi-time period data in a single low-income country. However, if the ICC is suitably low and the CAC is suitable high, at the time of analysis, we do not predict any difficulties. We will obtain this information from our observational pilot data gathered in January to May 2022 in all eight districts of the study. Feasibility data suggests the CAC is likely to be 1. Therefore, even with an extremely high intra-cluster correlation of 0.5, power would be close to 100%. We have used https://clusterrcts.shinyapps.io/rshinyapp/ for the calculations. As per Fig. 3, with a CAC of 1, power will be more than adequate with 1000 women per month per centre.

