## Assignment of interventions: allocation

### Sequence generation {16a}

The unit of randomisation in our trial is the cluster (a district), rather than individual women. Two clusters, Falaba and Bonthe, were paired before randomisation. The districts will first be allocated random area numbers, and the sequence of timing for receiving the CRADLE intervention will then be determined by computer-generated random numbers by the CRADLE statistician.

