## Statistical methods

### Statistical methods for primary and secondary outcomes {20a}

This is a type 2 hybrid implementation-effectiveness cluster randomised controlled trial in a stepped-wedge design that will allow us to simultaneously test our clinical intervention in the form of the CRADLE device and the effectiveness of our implementation strategy. This design is based on those described by Hussey and Hughes [29] and Curran et al. [30].

For our primary analysis method, we will use a new approach described by Thompson et al. [31, 32]. For this non-parametric within-period method, Monte Carlo permutation tests for stepped wedge trial designs are employed to calculate the confidence intervals and *P*-values. This is implemented in the Stata command “swpermute” [31]. Based on current statistical theory, this will provide the most accurate and reliable estimates of the intervention effect.

Thompson et al. [31] provide a non-parametric within-period method for correcting the *P*-values (and therefore the standard errors) for a valid regression model. The regression model (binomial, with a log link) that we propose to use will estimate the risk ratio for the effect of the planned intervention. It will include fixed effects for separate linear trends in each region, with a single step at the time the intervention is introduced into the district. As the method is robust to how the correlation structure is specified, further allowances for the data structure, as used in multi-level modelling, are not needed. Odds ratios will be given if models fail to converge when estimating risk ratios. Effects of treatment on primary outcomes will be estimated with 95% confidence intervals and significance at *P* < 0.05. As the primary endpoint is a composite, all the components will also be analysed in the same way. The effect of the intervention on primary and secondary outcomes will be analysed using multilevel logistic regression with random effects of centre and adjustments for fixed categorical effects of time. In addition, we will adjust for the availability of six common drugs: magnesium sulphate (MgSO_4_), ampicillin, gentamycin, metronidazole, oxytocin, and misoprostol, varying with time and district.

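### As written, the primary model adjusts by region, not by the randomised district, so stable district differences add variance that the power statement assumes away

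*Protocol article*

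**What the plan says.** Four places in the protocol article bear on this.

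- **Study setting {9}** defines the geography: "The country is divided into five administrative regions (Northern, Southern, Eastern, North-western, and Western) which are further subdivided into 16 districts". It then says "Each trial cluster is made up of a specific district in SL".
- **Sequence generation {16a}** confirms the unit: "The unit of randomisation in our trial is the cluster (a district), rather than individual women". It adds that "Two clusters, Falaba and Bonthe, were paired before randomisation".
- **Statistical methods {20a}** names a Monte Carlo permutation method as primary. Its regression is binomial with a log link and has "fixed effects for separate linear trends in each region, with a single step at the time the intervention is introduced into the district". Because the method is robust to the specified correlation structure, "further allowances for the data structure, as used in multi-level modelling, are not needed". Later in the same paragraph a multilevel logistic model with random effects of centre and categorical time is also named for the primary and secondary outcomes.
- **Sample size estimation {14}** takes CAC as likely to be 1 and concludes that "even with an extremely high intra-cluster correlation of 0.5, power would be close to 100" per cent.

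**The concern.** A stepped-wedge trial with eight clusters draws most of its precision from comparing each cluster with itself before and after crossover. That needs a term for each cluster's own level. The primary regression as worded has location terms only at a level above the cluster.

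Eight districts in at most five regions cannot each have their own line. At most four regions could hold a single trial district, so at least 8 − 4 = 4 districts share a line with another. Where two districts share a line, a stable difference between their event rates is not removed. It enters the intervention contrast with a sign and size set by which district happened to cross first.

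At stake is the ability to detect the 20% reduction that the Objectives section sets as the target, and the match between the planned analysis and the power claimed for it.

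**Working it through.** **Inputs from the protocol article.** Eight districts; 1000 deliveries per district per six weeks; 5% falling to 4% (RR 0.80, log RR −0.223); CAC 1; significance at 0.05 (Sample size estimation {14}, Statistical methods {20a}). ICCs shown: 0.01, 0.02 and 0.5 (Fig. 3 legend). One district crossing per step after a baseline gives 8 steps and 9 periods. If the Falaba–Bonthe pairing means a shared step, there are 7 steps and 8 periods.

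**Assumptions.** Two-sided test; equal cell sizes; log-normal district rates; region intercepts alongside region slopes; and the district-to-region grouping, which the article does not give.

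**Step 1: reproduce the stated power.** The Hussey–Hughes variance, with cell variance s² = (1 − ρ)p(1 − p)/m and district variance t² = ρp(1 − p), is

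Var = I·s²(s² + T·t²) / [(I·U − W)s² + (U² + I·T·U − T·W − I·V)t²].

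For 8 steps and 9 periods, U = 36 and W = V = 204. The coefficients are 8×36 − 204 = 84 and 1296 + 2592 − 1836 − 1632 = 420. Take p = 0.045 (midpoint of 5% and 4%), m = 1000 and ρ = 0.5. Then s² = 0.5×0.042975/1000 = 0.0000215 and t² = 0.0215. The SE is 0.00192, z = 0.01/0.00192 = 5.2, and power is 99.9% (99.8% with 7 steps). The stated figure reproduces. At ICC 0.01 the same formula gives 96% (94% with 7 steps).

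It reproduces because this formula includes the district effect. Once t² dominates, Var tends to I·T·s²/420, in which t² no longer appears. That cancellation is what makes an ICC of 0.5 harmless, and it needs a district term.

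**Step 2: power of the model as worded.** Trials were simulated with binomial counts, and the step was estimated on log cell rates. The permutation test was run over crossover orders (3000 trials per setting, 500 permutations each). District terms means an intercept and slope per district; region terms means an intercept and slope per region. The groupings were 3/2/2/1, 2/2/2/2, 2/2/2/1/1, 3/3/2 and 4/4.

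| ICC | District terms, 9 periods | Region terms, 9 periods | District terms, 8 periods | Region terms, 8 periods |
|---|---|---|---|---|
| 0.001 | 91% | 65–74% | 86% | 60–73% |
| 0.005 | 88% | 25–39% | 82% | 24–45% |
| 0.01 | 85% | 15–26% | 80% | 16–34% |
| 0.02 | 80% | 12–19% | 75% | 12–27% |

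Separate 9-period simulations agreed. At ICC 0.01 they gave 84–88% with district terms and 17–31% with region terms. At ICC 0.02 they gave 79–81% and 12–21%, and at ICC 0.001 they gave 89–93% and 64–74%.

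**Step 3: where the loss comes from.**
- With no district variation the region model has 95–98% power, so the loss is due entirely to stable district differences.
- At ICC 0.01 the SD of the log RR is 0.23–0.25 with region terms and 0.07 with district terms. Around a true RR of 0.80, 95% of estimates lie within 0.80×exp(±1.96×0.25) = 0.49 to 1.31, against 0.80×exp(±1.96×0.07) = 0.70 to 0.92.
- More deliveries do not help. With a district log-SD of 0.3 (about ICC 0.005), 2000 per cell leaves the region model near 33%, while the district model reaches 98%.
- A longer trial helps little. The dates in Trial status (23 May 2022 to 1 January 2024) span 588 days, or 588/42 = 14 periods. At ICC 0.01 that gives 29% against 95%.
- District intercepts are what matter. With region slopes kept, power at ICC 0.01 is 82–88%. With categorical period instead of slopes it is 84–89%.

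**Step 4: validity.** Under the null, the region model's permutation test rejected in 5.2% and 5.7% of trials in two simulations. Under RR 0.80 the mean log RR was about −0.22, the true value.

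**The case against.** The strongest reply is that region is loose wording for the cluster. The article also calls the cluster a group, a centre and an area. It gives regions no role in design or randomisation and never assigns a trial district to one. One trend with one step per cluster is a natural reading, and on it the power loss disappears. That may well be the intent. But the sentence uses region and district side by side, and Study setting defines them as different levels, so the text needs correcting either way.

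Second, the sentence says what the model will include, which need not be a full list, and the disclaimer mentions multilevel allowances rather than fixed terms. The absence of a district intercept is therefore a literal reading, not an explicit statement. An analysis plan may list more terms. Still, the article does fix the level of the trends and says no more is needed.

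Third, a random-centre logistic model is named for the same outcome, so a cluster-level term is planned somewhere. That does not change the method labelled primary. It leaves the section inconsistent on location terms.

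Two stronger readings are tempting. A reader might infer bias or false positives. The documents do not support that: permutation over the randomised order protects the P-value, and the estimate is centred on the truth. A reader might also infer one fixed fall in power. The article fixes no planning ICC and gives no district-to-region map, so only ranges can be given. The district differences it reports (population size, one district without a hospital) are not event rates.

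**Conclusion.** The point holds as a mismatch between the stated primary model, the unit of randomisation and the power claim. Read as written, the model is valid but imprecise, and its estimate depends heavily on the realised crossover order. Across both readings of the pairing and all groupings tried, power is about:

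- ICC 0.01: 15–34% with region terms, 80–88% with district terms
- ICC 0.02: 12–27% against 75–81%
- ICC 0.001: 60–74% against 86–93%

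These figures rest on the assumed groupings, log-normal district effects, equal cells, CAC 1 and region intercepts alongside the slopes. With one common intercept instead, power at ICC 0.01 is about 14–15%. If region was meant as district, what remains is a wording correction and a restatement of power. The place to correct is Statistical methods {20a}; the geography in Study setting is only the definition that exposes the problem.

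**What to change.** In Statistical methods {20a}:

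1. State that the primary log-binomial model has a fixed intercept for each of the eight districts, together with the time terms and the intervention step.
2. State the level of the time trends: district, region or common. If region was meant as district, correct the word.
3. Limit the sentence on further allowances to the validity of the permutation P-value.
4. Say how this model relates to the random-centre logistic model named for the same outcome, and which of the two is primary.

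In Sample size estimation {14}, restate power for the model actually used, with its ICC, number of periods and handling of the Falaba–Bonthe pair.

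The cost is a few lines of text and a few degrees of freedom. Eight district intercepts replace at most five region intercepts, against 8×9 = 72 district-periods. No new data are needed.

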## Interventions

### Explanation for the choice of comparators {6b}

Prior to transitioning to the CRADLE intervention, all women will be managed according to local guidelines (see https://mohs2017.files.wordpress.com/2018/04/sl-emonc-protocols-and-guidelines-a4-final.pdf to access national guidelines for emergency obstetric and newborn care). None of the districts will receive the intervention at time point 0. One district will be randomly allocated to receive the intervention at time point 1, whilst all the remaining areas contribute to the control at this time point. A second district is randomly allocated to the intervention at time point 2 and so on. Each randomisation cluster will cross over from the control to the CRADLE intervention at six-weekly intervals (see Fig. 2).

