### Outcomes {12}

Analysis of each outcome will be as a proportion of all deliveries during the six-week period within that district, as assessed from routinely collected data.

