#### Primary outcome measure

The primary outcome is the rate of a composite of maternal mortality, major maternal morbidity and fetal losses (with no double counting) occurring during pregnancy, labour or within 42 days of delivery, including at least one of:Maternal death (all-cause mortality)Eclampsia (occurrence of generalised convulsions with increased blood pressure in the absence of epilepsy or another condition predisposing to convulsions)Emergency hysterectomy (surgical removal of all or part of the uterus)Stillbirth (born without signs of life at or after 28 weeks of gestation)

The primary outcome measures will be assessed by the numbers of events reported at the district (or referral) hospital and the peripheral health units offering the highest level of care (defined as the 20% with the highest level facilities in each district).

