### Interim analyses {21b}

All analyses will adhere to the intention-to-treat principle, meaning that subjects will be analysed based on the treatment option they were assigned to at the centre when the event occurred. No additional analyses based on the per-protocol principle will be conducted.

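### Falaba refers mainly to Koinadugu's hospital but crosses over separately from it, and the protocol's rules conflict on how such a referral's exposure is labelled and do not say which district it belongs to.

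*Protocol article*

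**What the plan says.** All places are in the protocol article.

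- **Study setting {9}.** "Each trial cluster is made up of a specific district in SL", and Falaba and Koinadugu are both listed. On referral: "One district (Falaba) does not have a secondary hospital, and referrals from its satellite primary care centres go primarily to the secondary hospital in Koinadugu". Some of Falaba's referrals go to further adjoining districts, which are not named.
- **Sequence generation {16a}.** "Two clusters, Falaba and Bonthe, were paired before randomisation".
- **Explanation for the choice of comparators {6b}.** "Each randomisation cluster will cross over from the control to the CRADLE intervention at six-weekly intervals".
- **Outcomes {12}.** "Analysis of each outcome will be as a proportion of all deliveries during the six-week period within that district".
- **Primary outcome measure.** Outcomes are "assessed by the numbers of events reported at the district (or referral) hospital" and at the top 20% of peripheral units.
- **Plans for assessment and collection of outcomes {18a}.** The date of first presentation fixes the analysis period. The reason given is that a woman first seen before the crossover had not been exposed at that time. Referred women are noted in order to prevent double counting. Outcomes elsewhere are left out.
- **Interim analyses {21b}**, where the intention-to-treat sentence stands: "subjects will be analysed based on the treatment option they were assigned to at the centre when the event occurred".

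**The concern.** Two of the eight clusters are linked through one hospital, and they belong to different randomised units. Take a Falaba woman who first presents at a Falaba peripheral unit and has her event in Koinadugu's hospital. Section {18a} gives her period by first presentation but does not name her district. Section {21b} gives her exposure by the centre and time of the event. Between the two crossovers these rules can give her opposite exposure labels. Under {21b} her event may also enter Koinadugu's numerator, while the deliveries from which such events arise remain largely in Falaba's denominator.

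Two distortions could follow:

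1. With a stable referral share, events carry the wrong label in the discordant periods, which pulls the effect towards the null.
2. The training covers referral triggers, and the protocol expects referral to change. If Falaba's referral share rises at its own crossover, its counted events fall without any true effect, which pushes the estimate towards benefit.

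Separately, between the crossovers a Falaba woman meets one condition at her peripheral unit and the other at the hospital, whatever attribution rule is used.

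**Working it through.** **Inputs from the protocol.** Eight districts, six-weekly steps, 1000 deliveries per district-period, 5% falling to 4% (risk ratio 0.80), cluster autocorrelation 1, significance at 0.05 (taken as two-sided).

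**Assumptions.** The protocol gives no referral share, so f, the fraction of Falaba's events that occur in Koinadugu's hospital, is varied. Districts are taken as equal in size. Falaba and Bonthe are taken to cross together, giving seven steps and eight periods.

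**1. The plan's own figure.** A stepped-wedge generalised least squares variance with fixed period effects was used, with mean risk 0.045 and total variance 0.045 × 0.955 = 0.0430. At ICC 0.5, power is 99.9% with eight single steps and 99.8% with seven steps and the pair. The stated power of close to 100% is reproduced. At ICC 0.01 to 0.02 it is 96% and 94% respectively.

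**2. Crossover gap.** For two distinct positions among n steps, the expected gap is (n + 1)/3.

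- n = 7: 8/3 = 2.67 periods, or 2.67 × 6 = 16 weeks. The gap ranges from 1 to 6 periods.
- Discordant share: 2.67/8 = one third of periods, ranging from 1/8 to 6/8.
- If the pair does not cross together, n = 8: 9/3 = 3 periods, or 18 weeks, and 3/9 is again one third.

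**3. Mislabelled events under {21b}.** Roughly f × (1/3) × (1/8) of all trial events on average. This is 1.3% at f = 0.3, 2.1% at f = 0.5 and 3.8% at f = 0.9.

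**4. Effect on the pooled risk ratio.** Expected counts were fitted with a log-link model with district and period effects, over all 7 × 6 = 42 placements of the Falaba–Bonthe unit and Koinadugu. Falaba's moved events were added to Koinadugu's numerator and denominators were left unchanged.

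| Scenario | Mean fitted RR | Extreme placement |
|---|---|---|
| True RR 0.80, credited by first presentation (f = 0) | 0.800 | 0.800 |
| True RR 0.80, f = 0.5 throughout | 0.813 | 0.820 |
| True RR 0.80, f = 0.7 throughout | 0.818 | 0.826 |
| True RR 0.80, f = 0.9 throughout | 0.822 | 0.832 |
| No effect, f from 0.5 to 0.55 at Falaba's crossover | 0.993 | 0.986 |
| No effect, f from 0.5 to 0.6 | 0.985 | 0.971 |
| No effect, f from 0.5 to 0.7 | 0.971 | 0.943 |
| True RR 0.80, f from 0.5 to 0.6 | 0.802 | 0.795 to 0.812 |

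Replacing the period effects with district-specific linear trends, closer to the model in section {20a}, gives means of 0.986 and 0.971 for the null rows at 0.6 and 0.7. If Falaba is half the size of the others, the null row at 0.6 becomes 0.992.

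**5. Apparent baseline rates.** At f = 0.5, 50 events per 1000 in each district would appear as 50 − 25 = 25 (2.5%) in Falaba and 50 + 25 = 75 (7.5%) in Koinadugu.

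**The case against.** The strongest reply is that the protocol does not say Falaba's events are counted in Koinadugu. The words in brackets in the primary outcome section, on the referral hospital, can cover a district whose hospital lies elsewhere. Referred women are noted, and the reason given for the first-presentation rule is exposure at initial contact. Only the sentence in {21b} points the other way, and it does not define the centre. This stands. A reader might infer that misattribution is certain, but the documents support only an unstated district rule and a conflict between {18a} and {21b}. That conflict goes beyond detail left to an analysis plan, because the two stated rules give different answers for the same woman.

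A reader might also infer that the artefact could equal the whole target effect. In Falaba alone, a rise in referral from 50% to 60% takes its counted events from 25 to 20, a ratio of 0.80. That is a before-and-after ratio in one district under an assumed shift, and the pooled figure is 0.985. Nor would the shift look like benefit in both districts. Koinadugu's count rises from 75 to 80, and it does so at Falaba's crossover, not its own.

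The two mechanisms act in opposite directions and can nearly cancel (0.802 against 0.80). Falaba has the fewest peripheral units (50), so its weight may be smaller than assumed. Some movement across district lines is expected in a pragmatic trial. The absence of a sensitivity analysis from this article is not itself a fault, since an analysis plan may hold one.

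**Conclusion.** The point holds as a conflict between stated rules in a design that links two clusters. Falaba's main referral hospital lies in a district that crosses at another step, {18a} and {21b} disagree on when exposure is fixed, and no section assigns the district.

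If {21b} is followed literally, the pooled bias is modest. A true risk ratio of 0.80 is estimated as 0.81 to 0.82 (worst 0.83) at constant shares of 50 to 90%. A null effect is estimated as about 0.985 (lowest 0.97) if the share rises from 50% to 60%. These figures rest on equal district sizes, assumed shares and a fixed-effects log-link fit, not the planned permutation method. The direction cannot be assumed conservative.

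The rule should be settled before analysis, because choosing it after seeing the results would be a data-dependent decision.

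**What to change.** 1. Reconcile the primary outcome section, {18a} and {21b}: assign each primary event, for numerator, period and exposure, to the district and date of first presentation, wherever the event occurs. This covers Falaba women treated in Koinadugu and those treated in other neighbouring trial districts. State also what happens to Falaba events in a hospital outside the trial districts, which the rule leaving out outcomes elsewhere would now drop.
2. Have the existing referral note record the originating district. {18a} does not say that it does so. If the originating facility is already recorded, no new data are needed.
3. Keep the denominator as deliveries in each district. Moving individual deliveries is unnecessary and not clearly feasible, since section {20b} says that detailed information on total deliveries cannot be collected.
4. Pre-specify a sensitivity analysis that treats Falaba and Koinadugu as one catchment and leaves out the periods in which their allocations differ.

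The cost is a few sentences, one field in the referral note if it is not already there, and one further model run. The sensitivity analysis loses some precision through the dropped periods. Under the main analysis, mixed exposure between the two crossovers remains, and wording cannot remove it.
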